**A. Trial registration:**

|                         |                                                                                                                                                                                                                                                                                                                                                                                                                                                                                                                                                          |
|-------------------------|----------------------------------------------------------------------------------------------------------------------------------------------------------------------------------------------------------------------------------------------------------------------------------------------------------------------------------------------------------------------------------------------------------------------------------------------------------------------------------------------------------------------------------------------------------|
| Primary registry and ID | ClinicalTrials.gov NCT05821023                                                                                                                                                                                                                                                                                                                                                                                                                                                                                                                           |
| Source of funding       | NIA R01AG066741                                                                                                                                                                                                                                                                                                                                                                                                                                                                                                                                          |
| Sponsor                 | Johns Hopkins University                                                                                                                                                                                                                                                                                                                                                                                                                                                                                                                                 |
| Human subjects review   | IRB00283392                                                                                                                                                                                                                                                                                                                                                                                                                                                                                                                                              |
| Contact                 | [name] MD; [contact] ; [name]                                                                                                                                                                                                                                                                                                                                                                                                                                                 |
| Study description       | This is an online survey experiment with data collection over 2 time points two weeks apart. This is Aim 2 of a three-aim R01 project; overall project goal is to better understand how messages from different sources interact to affect older women's breast cancer screening decisions. In this current project, the investigators propose to test the effect of combined exposure to a clinician message + a message from another source (i.e. family/friend or media) on older women's breast cancer screening beliefs, attitudes, and intentions. |
| Health conditions       | Breast cancer screening                                                                                                                                                                                                                                                                                                                                                                                                                                                                                                                                  |
| Study design            | Randomized controlled interventional study with parallel assignment to 1 of 6 groups                                                                                                                                                                                                                                                                                                                                                                                                                                                                     |
| Interventions           | Group 1 – no message exposure;
Group 2 – single clinician message at Wave 1 on screening cessation; no message at Wave 2.                                                                                                                                                                                                                                                                                                                                                                                                                             |

|                       |                                                                                                                                                                                                                                                                                                                                                                                                                                                                                                                                          |
|-----------------------|------------------------------------------------------------------------------------------------------------------------------------------------------------------------------------------------------------------------------------------------------------------------------------------------------------------------------------------------------------------------------------------------------------------------------------------------------------------------------------------------------------------------------------------|
|                       | Group 3 – message from news story at Wave 1 on screening cessation; message from clinician at Wave 2 on screening cessation.
Group 4 – message from family member at Wave 1 on screening cessation; message from clinician at Wave 2 on screening cessation.
Group 5 – message from news story at Wave 1 on screening continuation; message from clinician at Wave 2 on screening cessation.
Group 6 – message from family member at Wave 1 on screening continuation; message from clinician at Wave 2 on screening cessation. |
| Outcome measures      | Primary outcomes: support for stopping screening for a hypothetical older woman in the survey vignette
Secondary or other pre-specified outcomes: screening intention for participants; breast cancer screening attitudes; perceived message effectiveness; emotional response; negative perceptions of mammograms; awareness of screening harms; confusion or backlash about conflicting messages                                                                                                                                    |
| Eligibility           | Inclusion criteria: 65 years; female; part of an online survey panel called KnowledgePanel; able to complete survey in English.
Exclusion criteria: personal history of breast cancer                                                                                                                                                                                                                                                                                                                                                 |
| Study start date      | May 12, 2023                                                                                                                                                                                                                                                                                                                                                                                                                                                                                                                             |
| Study completion date | June 19, 2023                                                                                                                                                                                                                                                                                                                                                                                                                                                                                                                            |

## B. Background and Objectives (Specific Aims)

Breast cancer is the most common life-threatening cancer in women. Mammography screening may decrease cancer-related mortality and morbidity, but the potential benefits of screening are often delayed for many years while significant harms, such as over-diagnosis and over-treatment of clinically unimportant cancers, can occur in the short-term. Despite guidelines recommending against routine breast cancer screening in older women with limited life expectancies, many of these older women continue to be screened. The overarching premise of this project is that clinician-patient communication holds promise to promote appropriate screening cessation and reduce over-screening in older women but its impact may be weakened by conflicting messages from other sources. Better understanding the interplay between messages from clinical and non-clinical sources is crucial to inform interventions.

Clinicians are an important and trusted source of information regarding cancer screening and their recommendations strongly influence patients' screening behavior. Our prior research suggests that a) clinicians are increasingly willing to recommend that older patients forgo screening and b) older patients are increasingly willing to accept these recommendations in the setting of a trusting relationship. However, clinicians reported barriers to stopping routine cancer screening: one barrier in particular is that patients often receive contradictory (and largely pro-screening) messages from their family, friends, or the media.

Indeed, clinician-patient communication does not occur in a vacuum but rather happens in the setting of patients' social relationships and the broader media landscape. Prior research found that experiences with friends or family members who had screening-detected

early stage breast cancers were associated with significant increase in women's own intentions to get screened (Odds Ratio 2.89). Also, media coverage has often focused on screening's benefits and screening initiation rather than the decision about stopping screening. For example, we found that among televised news stories reporting on the American Cancer Society's 2015 breast cancer screening recommendations, 94.4% reported on when screening should start, but only 3.4% reported that life expectancy should be used to decide whether or not to stop screening.

In this context, even when clinicians are willing and able to discuss screening cessation with older women, the impact of their messages may be reduced or negated altogether by competing information. Conversely, if messages from the media and patients' social networks (i.e. family/friends) were to align with that from the clinicians, they could have a powerful synergistic influence to reduce over-screening. Before an effective messaging intervention can be developed to reduce over-screening, it is critical to first identify which messages/messengers are likely to have the greatest impact. This project addresses these knowledge gaps by examining how messages from clinicians, social networks, and media, separately and together, impact older women's screening intentions, with the goal of informing a messaging intervention to reduce over-screening.

(Prior work) Aim 1 – To establish which messages intended to reduce breast cancer over-screening are considered most credible among older women. Establishing message credibility is important before assessing message impact since messages that are not credible are more likely to be rejected. In a national online survey, we will randomize 600 older women (age 65+ years) to read and evaluate the credibility of different types of messages (e.g. evidence, anecdote) that describe the harms of over-screening. We will systematically vary the information source - clinician, family/friend, or media - for each message.

**(Current project) Aim 2 – To identify the combined effects of consistent and conflicting messages from different sources—including clinicians, social relationships, and media—on breast cancer screening beliefs, attitudes, and intentions over time.** Using top-rated messages from Aim 1, we will conduct a two-wave online survey experiment with 3000 older women from a nationally representative panel. The two waves will include a clinician message intended to reduce over-screening (i.e. mentions harms of over-screening, supports screening cessation) and a non-clinician message. We will vary whether the non-clinician message is from family/friend or the media; we will also vary whether the non-clinician message supports or opposes screening cessation. We hypothesize that the effect of clinician message on screening intentions will be strengthened when paired with consistent messages and weakened when paired with conflicting messages.

(Next step) Aim 3 – To engage multi-disciplinary stakeholders to devise message delivery strategy for subsequent intervention. We will conduct focus groups with 30-40 stakeholders representing the end users of the messaging strategies, including clinicians, health system administrators, older women, caregivers, community leaders, advocacy group representatives, and health journalists. Focus groups will help devise strategies to deliver, in a real-world context, the messages from Aim 2 that most effectively reduced screening intentions.

This innovative work will produce much needed data on effective strategies to communicate the rationale for stopping cancer screening when harms outweigh the benefits. The results will directly inform a novel communication intervention, as next step, to reduce breast cancer over-screening among older women.

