**C.4. Interventions and Choice of comparator:**

We will randomly assign women meeting eligibility to 6 groups (Table 1). The experimental groups 3-6 will read a message at Wave 1 that may be from either family/friend or the media followed by a second message from a clinician one to two weeks later at Wave 2, as research suggests that message decay occurs in 1-2 weeks. By presenting the non-clinician message first, we aim to mimic the real-world scenario where patients are often exposed to information from their family, friends and/or the media before a clinic visit.

The clinician message will be directed at reducing over-screening, mentioning the harms of over-screening and supporting screening cessation. We will systematically vary the non-

clinician message to be either consistent with the clinician message (also mentions harms of over-screening and supports screening cessation) or conflicting (mentions benefits of screening, supports continued screening and opposes screening cessation). We include a no-exposure control group (Group 1) where the participants read no message at either time point. We also include a single exposure group that reads only the clinician message (Group 2).

Table 1. Aim 2 experimental design

| Group # | Group type                | Wave 1        |                    | Wave 2     |                |
|---------|---------------------------|---------------|--------------------|------------|----------------|
|         |                           | Source        | Content            | Source     | Content        |
| 1       | Control (no exposure)     | No message    | No message         | No message | No message     |
| 2       | Control (single exposure) | Clinician     | Stop screening     | No message | No message     |
| 3       | Experimental              | Media         | Stop screening     | Clinician  | Stop screening |
| 4       | Experimental              | Family/Friend | Stop screening     | Clinician  | Stop screening |
| 5       | Experimental              | Media         | Continue screening | Clinician  | Stop screening |
| 6       | Experimental              | Family/Friend | Continue screening | Clinician  | Stop screening |

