#### **C.6. Statistical methods and sample size.**

The main analysis focuses on the primary outcome assessed at Wave 2 with the independent variables being the randomly assigned message/messenger combinations. The primary goal is to compare the experimental groups (Groups 3-6) at Wave 2 with both control groups to assess the combined effect of consistent and conflicting messages over time. We hypothesize that the participants who read consistent messages both directed at reducing over-screening (Groups 3,4) will have higher support and higher intentions to stop screening than participants who read clinician message alone (Group 2); the participants who read conflicting messages (Groups 5,6) will have lower intentions to stop screening than participants who read clinician message alone (Group 2). We will compare the mean scores across groups using ANOVA and adjust for multiple comparisons. We will conduct exploratory analyses by key covariates, including age, predicted life expectancy based on health and functional status, to examine the impact of messaging within these subgroups.

Power calculations are based on preliminary data in which we asked 41 patients 65+ about willingness to stop routine cancer screening if recommended by their clinician. Based on the distribution of responses from this preliminary data, we estimate that with 400 participants randomized to each group at Wave 2, we will have 80% power to detect a 0.30 point difference for the primary outcome. The survey company Ipsos that manages and maintains the KnowledgePanel affirms that, through their recruiting strategy and based on their past experience, 20% attrition or less is expected between the two waves over 1-2 weeks. Assuming 20% attrition, we will target 500 per group at Wave 1.

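### Aim 2 hypothesises that other messages modify the clinician message's effect, but the Wave 2 comparison with Group 2 estimates a combined-sequence effect and cannot isolate modification

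*Protocol*

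**What the plan says.** Section B puts the Aim 2 hypothesis as a change in the clinician message's own effect: "the effect of clinician message on screening intentions will be strengthened when paired with consistent messages and weakened when paired with conflicting messages". The background in the same section says that, if media and family messages agreed with the clinician, "they could have a powerful synergistic influence to reduce over-screening", and that competing information may reduce or cancel the clinician's impact.

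C.6 sets the test. "The main analysis focuses on the primary outcome assessed at Wave 2", and Groups 3-6 are compared with both control groups "to assess the combined effect of consistent and conflicting messages over time". Groups 3,4 are expected to score higher than Group 2. Participants in Groups 5,6 "will have lower intentions to stop screening than participants who read clinician message alone (Group 2").

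The exposures are timed differently. Section A gives Group 2 a "single clinician message at Wave 1 on screening cessation; no message at Wave 2". C.4 gives Groups 3-6 a media or family message at Wave 1, "followed by a second message from a clinician one to two weeks later at Wave 2". C.4 justifies the interval by saying that "research suggests that message decay occurs in 1-2 weeks". It gives no retained fraction and exempts no source.

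Table 1 has no arm with a non-clinician message at Wave 1 and nothing at Wave 2, and none with nothing at Wave 1 and the clinician message at Wave 2. Table 2 lists no separate Wave 2 measurement ahead of the clinician message.

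**The concern.** A modification hypothesis needs an estimate of how much the clinician message moves opinion after another message, set against how much it moves opinion alone. The comparison in C.6 is of end-point levels after different sequences. Groups 3,4 can end above Group 2 because the first message has not worn off, or because they have just read the clinician message while Group 2 read it one to two weeks earlier. Neither means that the clinician message worked better.

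The distinction matters because section B says the results will feed directly into a communication intervention. If messages simply add up, the lesson is about the number and timing of exposures. If one message changes how another is received, the lesson is about coordinating sources. The stated comparison cannot tell these apart.

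**Working it through.** **The plan's own figures.** 400 / (1 - 0.20) = 500 per group, and 6 x 500 = 3000, so the attrition step reproduces. C.6 claims 80% power for 0.30 points with 400 per group but states neither the SD nor alpha. At an assumed two-sided 0.05 the implied SD is 0.30 / [(1.960 + 0.842) x sqrt(2/400)] = 1.514. That SD is used below, unadjusted for multiplicity. The SE of a two-group difference is 1.514 x sqrt(2/400) = 0.107.

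**What the contrast contains.** Let C be the fresh effect of the clinician message, M the signed fresh effect of the non-clinician message, rC and rM the fractions left at Wave 2, and I the modification. Relative to Group 1 at Wave 2:

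- Group 2: C x rC
- Groups 3-6: C + M x rM + I
- Difference from Group 2: C(1 - rC) + M x rM + I

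The first term is recency, the second is carry-over, and only I is the Aim 2 hypothesis.

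**Zero modification (I = 0).** The effect sizes and retained fractions are assumptions. Each row compares 400 with 400; M is positive for Groups 3,4 and negative for Groups 5,6.

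| C | Size of M | rC | rM | Groups 3,4 minus Group 2 | Groups 5,6 minus Group 2 |
|---|---|---|---|---|---|
| 0.30 | 0.30 | 1 | 1 | +0.30 (80% significantly higher) | -0.30 (80% significantly lower) |
| 0.30 | 0.30 | 0.5 | 0.5 | +0.30 (80% higher) | 0.00 (2.5% lower) |
| 0.30 | 0.30 | 0 | 0 | +0.30 (80% higher) | +0.30 (80% higher) |
| 0.30 | 0.50 | 0.5 | 0.5 | +0.40 (96% higher) | -0.10 (15% lower) |
| 0.50 | 0.30 | 0.5 | 0.5 | +0.40 (96% higher) | +0.10 (15% higher) |
| 0.30 | 0.30 | 1 | 0.5 | +0.15 (29% higher) | -0.15 (29% lower) |

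For Groups 3,4 recency and carry-over have the same sign. With C = M and equal retention r the sum is C(1 - r) + C x r = C, whatever r is. For Groups 5,6 they oppose each other, and a false weakening needs the size of M x rM to exceed C(1 - rC).

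**Can the Wave 1 data rescue it?** A natural candidate is the Wave 2 minus Wave 1 change in Groups 3,4 or 5,6, less the same change in Group 1, set against Group 2 minus Group 1 at Wave 1. Its expectation is (C + M x rM + I - M) - C = I - M(1 - rM). Unless nothing decays, it is biased against the hypothesis in both pairs.

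To size the bias, assume SD 1.5, within-person correlation 0.6, 400 per group and the pair pooled (800). The variance is 2 x 2.25 x 0.4/800 + 2.25 x (5 - 4 x 0.6)/400 + 2.25/400 = 0.0225, so the SE is 0.15. With M of size 0.6 and I = 0, the bias is 0.30 at half retention, which is significant in the wrong direction in about 51% of trials. At one-third retention the bias is 0.40, significant in the wrong direction in about 76%.

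**What isolating I would take.** The two missing kinds of arm would allow a four-cell contrast with SE 1.514 x sqrt(4/400) = 0.151. At 400 per cell, power for a 0.30-point modification is 51%, and the difference detectable with 80% power is 0.42. About 800 per cell at Wave 2 (800/0.8 = 1000 at Wave 1) would be needed for 0.30.

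**The case against.** The best defence is that the trial never set out to estimate an interaction. The study description and the Aim 2 heading speak of combined exposure and combined effects, C.6 names the combined effect as its goal, and the C.6 hypotheses are level comparisons that the contrast tests directly. The Aim 2 sentence could be plain language for the same thing. The synergy and cancellation language is background and conditional.

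Much of this stands. The contrast is sound for the target C.6 names. A reader might infer that the trial will report additive effects as synergy or negation, but no passage says so. What does not stand is the Aim 2 sentence: it makes the clinician message's effect the thing that changes, and C.6 offers no other test of it. A statistical analysis plan, not shown here, might add contrasts, but none can isolate modification in these six arms without an assumption about decay of the non-clinician message, whose retention no arm observes.

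A reader might also infer that carry-over alone yields the whole predicted pattern, false weakening included. With effects of 0.6, SD 1.5, Groups 5,6 pooled against Group 2 and half the Wave 1 message retained, the difference is -0.30 and significant about 90% of the time (about 59% at one third). That holds only if Group 2's clinician message does not decay at all, and the decay statement in C.4 gives no support for such an exemption. With equal decay the same settings give 0.00 at half retention (significantly lower in about 3%) and +0.20 at one third (significantly higher in 59%).

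**Conclusion.** The point holds as a mismatch between the Aim 2 hypothesis and its only stated test. The Group 2 comparison does not isolate modification, and no arm in Table 1 allows it to be isolated.

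For Groups 3,4 a false strengthening is to be expected whenever both messages push towards stopping, except where Group 2's message keeps its full effect and the other message keeps none. With effects of 0.30 and equal decay it equals the protocol's own target difference. That row's 80% follows from the protocol's power statement; the other percentages rest on the implied SD of 1.514, two-sided 0.05 and no multiplicity adjustment, and an adjustment at that SD would lower them.

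For Groups 5,6 no direction can be claimed. The contrast may show false weakening, nothing or the reverse, and by the same token may hide real weakening. The effect sizes and retained fractions are assumptions throughout. The structural conclusion does not depend on them.

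**What to change.** Reword the Aim 2 hypothesis in section B to match C.6: at Wave 2, Groups 3,4 have higher, and Groups 5,6 lower, support for stopping screening than the single-exposure Group 2. Name the same outcome in both places, since the Aim 2 sentence refers to intentions while the main analysis uses the primary outcome, support for cessation in a hypothetical patient.

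Add to C.6 that this comparison estimates the effect of the whole message sequence, including the different timing of the clinician message, and will not be interpreted as strengthening, weakening, synergy or negation of that message.

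Do not let a Wave 2 minus Wave 1 increment contrast carry the modification claim. At most it is a descriptive sensitivity analysis with its bias under message decay stated.

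The cost is a more modest claim, with no new data or participants. Keeping the modification claim would instead require the missing arms and roughly double the group size.
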